## 9.2. Inclusion Criteria/Exclusion Criteria

### 9.2.1. Inclusion Criteria

- 1) Young subjects: Healthy Korean or Caucasian volunteers between 19 and 45 years of age at the screening visit

Elderly subjects: Healthy Korean volunteers over 65 years and under 85 years of age at the screening visit

※ Caucasian who were born in Europe, have lived outside Europe for less than 10 years, and both parents and grandparents were of European origin.

- 2) Women: Except for surgical infertility (bilateral fallopian tube occlusion, hysterectomy, bilateral salpingectomy, bilateral oophorectomy, etc.), those who tested negative in the urine pregnancy test (hCG) performed at screening
- 3) Subjects with body weight between 55.0 kg and 90.0 kg and Body Mass Index (BMI) between 18.0 kg/m^2 and 30.0 kg/m^2 at the screening visit

※ Body Mass Index = body weight(kg)/ [height(m)]

- 4) Subjects who completely understand the nature of study and make a voluntary decision to participate in this clinical study and provide the informed consent.

- 5) Subjects who are considered to be suitable to participate in this study based on physical examination, clinical laboratory test results and medical history

#### 9.2.2. Exclusion Criteria

- 1) Subjects with a clinical evidence or history of hepatic, renal, neurologic, immunologic, respiratory, endocrine, hematologic, oncologic, cardiovascular, psychiatric disease (mood disorders, obsessive-compulsive disorder, etc.) (However, in the case of an elderly person with a history of mild disease, participation is possible if the researcher determines that the drug can be discontinued at least 2 weeks before the expected first dose or 5 times or more before the half-life.)
- 2) Subjects with a history of gastrointestinal disease (e.g., gastrointestinal ulcers, gastritis, stomach cramp, gastroesophageal reflux disease, Crohn's disease, etc.) or surgery (except for simple appendectomy or herniotomy), which can influence the safety and pharmacokinetic evaluation of investigational drugs
- 3) For all women of childbearing age, except for surgical infertility, those who are pregnant, may be pregnant, or are lactating
- 4) Subjects with clinically significant abnormalities in the neurological examination performed at the screening visit
- 5) Subjects with any of the following vital signs at the screening visit
  - ✓ Systolic blood pressure (SBP):  $< 90$  mmHg or  $> 140$  mmHg
  - ✓ Diastolic blood pressure (DBP):  $< 50$  mmHg or  $> 90$  mmHg
  - ✓ Heart rate:  $< 50$  bpm or  $> 90$  bpm
- 6) Subjects with any of the following clinical laboratory test results at the screening visit
  - ✓ AST, ALT:  $> \text{upper normal limit} \times 1.5$
  - ✓ Total bilirubin:  $> \text{upper normal limit} \times 1.5$
  - ✓ CPK:  $> \text{upper normal limit} \times 1.5$
  - ✓ Creatinine clearance calculated by CKD-EPI equation:  $< 60$  mL/min/1.73m^2
  - ✓ Subjects with a positive result in the serology test (syphilis test, Hepatitis B surface antigen, Hepatitis C antibody, Human immunodeficiency virus(HIV) antibody)
- 7) Subjects with any of the following ECG results at the screening visit
  - ✓ PR  $> 210$  msec
  - ✓ QRS complex  $> 120$  msec
  - ✓ QTcB  $> 450$  msec
  - ✓ Other, clinically significant arrhythmias
- 8) Subjects with a history of hypersensitivities including drug allergies (caused by aspirin, antibiotics, etc.), or a history of clinically significant hypersensitivities
- 9) Subjects with a history of alcohol or drug abuse, or with positive reaction to any drug of concern for abuse/misuse at the urine drug screening test
- 10) Subjects who had taken or are expected to take any prescription drug or herbal medicine within 2 weeks or any over the counter (OTC) drug within 1 week prior to the first administration day (however, subjects fulfilling other conditions could participate in the study at the investigator's discretion)

- 11) Subjects who had taken an inducer or inhibitor of drug metabolism such as barbiturates etc. within 1 month prior to the first administration day
- 12) Subjects who had participated in another clinical study (including bioequivalence studies) within 6 months prior to the first administration day
- 13) Subjects who had donated whole blood or component blood, or received transfusion within 3 months prior to the first administration day
- 14) Subjects who drink continuously (more than 21 units/week, 1 unit = 10 g of pure alcohol) or are unable to stop drinking during the period from 3 days prior to the first administration day to the end of the study
- 15) Smokers(except for whom quitted smoking prior to the first administration day for at least 3months) or who cannot stop smoking during the period from 3 months prior to the first administration day to the end of the study
- 16) Subjects who cannot stop taking grapefruit or food containing grapefruit during the period from 3 days prior to the first administration day to the end of the study
- 17) Subjects who have taken excessive amounts of caffeine (> 5 units/day) on a continuous basis or who cannot stop taking caffeine or food containing caffeine (coffee, tea(black tea, green tea, etc.), carbonated drink, coffee-flavored milk, nutritional tonics, etc.) during the period from 3 days prior to the first administration day to the end of the study
- 18) During the entire study period and for at least 3months after the last administration of the investigational drug, subjects who are unable to use an appropriate, medically accepted double contraception method or medically acceptable contraceptive method for themselves or their spouse or partner and who do not agree not to donate sperm by that period.
  - ※ Medically acceptable contraceptive methods
    - ✓ Use of an intrauterine device with a proven rate of pregnancy failure in the spouse (or partner)
    - ✓ Simultaneous use of a barrier contraception (for male or female) and spermicide
    - ✓ Surgery of the person himself or his spouse(or partner) (vasectomy, salpingectomy/ligation, hysterectomy)
- 19) Otherwise, subjects judged by the investigator to be inappropriate for inclusion in the study

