|  | 
 
4) Subjects with clinically significant abnormalities in the neurological examination performed at the screening visit
 
5) Subjects with any of the following vital signs at the screening visit 
 
✓ Systolic blood pressure (SBP): < 90 mmHg or > 140 mmHg
 
✓ Diastolic blood pressure (DBP): < 50 mmHg or > 90 mmHg
 
✓ Heart rate: < 50 bpm or > 90 bpm
 
 
 
6) Subjects with any of the following clinical laboratory test results at the screening visit 
 
✓ AST, ALT: > upper normal limit × 1.5
 
✓ Total bilirubin: > upper normal limit × 1.5
 
✓ CPK: > upper normal limit × 1.5
 
✓ Creatinine clearance calculated by CKD-EPI equation: < 60 mL/min/1.73m^2
 
✓ Subjects with a positive result in the serology test (syphilis test, Hepatitis B surface antigen, Hepatitis C antibody, Human immunodeficiency virus(HIV) antibody)
 
 
 
7) Subjects with any of the following ECG results at the screening visit 
 
✓ PR > 210 msec
 
✓ QRS complex > 120 msec
 
✓ QTcB > 450 msec
 
✓ Other, clinically significant arrhythmias
 
 
 
8) Subjects with a history of hypersensitivities including drug allergies (caused by aspirin, antibiotics, etc.), or a history of clinically significant hypersensitivities
 
9) Subjects with a history of alcohol or drug abuse, or with positive reaction to any drug of concern for abuse/misuse at the urine drug screening test
 
10) Subjects who had taken or are expected to take any prescription drug or herbal medicine within 2 weeks or any over the counter (OTC) drug within 1 week prior to the first administration day (however, subjects fulfilling other conditions could participate in the study at the investigator's discretion)
 
11) Subjects who had taken an inducer or inhibitor of drug metabolism such as barbiturates etc. within 1 month prior to the first administration day
 
12) Subjects who had participated in another clinical study (including bioequivalence studies) within 6 months prior to the first administration day
 
13) Subjects who had donated whole blood or component blood, or received transfusion within 3 months prior to the first administration day
 
14) Subjects who drink continuously (more than 21 units/week, 1 unit = 10 g of pure alcohol) or are unable to stop drinking during the period from 3 days prior to the first administration day to the end of the study
 
15) Smokers (except for whom quitted smoking prior to the first administration day for at least 3 months) or who cannot stop smoking during the period from 3 months prior to the first administration day to the end of the study
 
16) Subjects who cannot stop taking grapefruit or food containing grapefruit during the period from 3 days prior to the first administration day to the end of the study
 
17) Subjects who have taken excessive amounts of caffeine (> 5 units/day) on a continuous basis or who cannot stop taking caffeine or food containing caffeine (coffee, tea(black tea, green tea, etc.), carbonated drink, coffee-flavored milk, nutritional tonics, etc.) during the period from 3 days prior to the first administration day to the end of the study
 
18) During the entire study period and for at least 3 months after the last administration of the investigational drug, subjects who are unable to use an appropriate, medically accepted double contraception method or medically acceptable contraceptive method for themselves or their spouse or partner and who do not agree not to donate sperm by that period. 
 
✗ Medically acceptable contraceptive methods 
 
✓ Use of an intrauterine device with a proven rate of pregnancy failure in the spouse (or partner)
 
✓ Simultaneous use of a barrier contraception (for male or female) and spermicide
 
✓ Surgery of the person himself or his spouse(or partner) (vasectomy, salpingectomy/ligation,
 
 
 
 
 
 |

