administration of the test substance to rats at a dose of 50-200 mg/kg daily for 2 weeks, there were no deaths. As a result of oral administration to rats at doses of 30, 50, 75 and 100 mg/kg once daily for 4 weeks, histopathological changes due to administration of the test substance were observed in the kidneys, bladder, testis, epididymis and lungs. Renal epithelial hyperplasia and inflammatory cells infiltration in the renal pelvis observed in the male and female dose groups of 75 mg/kg or more, germ cell degeneration/loss and seminiferous tubules atrophy observed in the male dose groups of 75 mg/kg or more, and vacuole/degeneration of outer medullary tubules and basophilic tubules observed in the female dose groups were judged to be adverse effects due to administration of the test substance. Proximal tubular hyaline granules in the kidney, basophilic tubules, testicular germ cell degeneration/loss, and alveolar macrophage aggregation in the lungs(females) were observed even after a 2-week recovery period. Accordingly, in repeated administrations of rats for 4 weeks, the NOAEL(No Observed Adverse Effect Level) was determined to be 50 mg/kg/day for males and 30 mg/kg for females. As a result of repeated oral administrations of 0, 25, 50 or 100 mg/kg/day for 2 weeks to Cynomolgus Monkey, a dying condition or mortality was observed in male and female dose groups of 100 mg/kg/day and in male dose group of 50 mg/kg/day, and a distal tubule/collecting duct dilatation and papillary duct epithelial cell hypertrophy related to the test substance were observed in male and female dose groups of 100 mg/kg/day. As a result of repeated oral administrations of KDS2010 in monkeys at doses of 0, 10, 20, and 40 mg/kg for 4 weeks and observation of recovery for 2 weeks, there were no adverse effects related to the test substance and the NOAEL was judged as 40 mg/kg for both males and females. As a result of the safety pharmacology test, no effect of the test substance was observed in the tests to evaluate the effects of central nervous system, respiratory system, and cardiovascular system, and the IC50 in the hERG assay was  $7.8 \pm 1.7 \mu\text{M}$ . As a result of the genetic toxicology, the reverse mutation test, the chromosomal aberration assay, and the micronucleus assay were all negative.

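### Read literally, exclusion 18 makes inability to use contraception and refusal to forgo sperm donation cumulative, so neither alone excludes a man, and its result for fertile women is undefined

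*Protocol*

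**What the plan says.** Exclusion 18 in Protocol section 9.2.2 covers the whole study and at least three months after the last dose. Its first condition describes "subjects who are unable to use an appropriate, medically accepted double contraception method or medically acceptable contraceptive method for themselves or their spouse or partner". The join to the second condition reads "contraceptive method for themselves or their spouse or partner and who do not agree not to donate sperm by that period", and the synopsis ends in the same way: "and who do not agree not to donate sperm by that period". Both places use the same connector, and no other section restates the rule.

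A list of acceptable methods follows. One item is "Use of an intrauterine device with a proven rate of pregnancy failure in the spouse (or partner". Another is a barrier method, for either sex, combined with spermicide. The third is surgery on the person or on the spouse or partner, with male and female procedures named.

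Women may enrol. Apart from those who are surgically infertile, section 9.2.1 accepts "those who tested negative in the urine pregnancy test (hCG) performed at screening". Exclusion 3 removes women of childbearing age "those who are pregnant, may be pregnant, or are lactating". Exclusion 19 lets the investigator exclude anyone judged unsuitable.

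**The concern.** An eligibility rule is applied at screening as it is written. If both conditions must hold before a subject is excluded, inability to use contraception is not enough by itself, and neither is refusal of the sperm-donation undertaking. For a fertile woman, the second condition asks about something that does not apply to her, so two screeners could reach opposite answers from the same text.

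The rule has a purpose within this protocol. Section 5.1.3 reports "germ cell degeneration/loss and seminiferous tubules atrophy observed in the male dose groups of 75 mg/kg or more" in the 4-week rat study, and germ cell degeneration or loss was still seen after a 2-week recovery. Those findings lie above the stated male NOAEL of 50 mg/kg/day and do not predict harm in this trial. They do show why the contraception and sperm-donation conditions should be unambiguous.

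**Working it through.** The protocol gives no figure for this rule, so there is none to reproduce. The check is one of logic.

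**Inputs**
- A: unable to use an accepted contraceptive method (exclusion 18, first condition).
- B: does not agree to refrain from sperm donation (exclusion 18, second condition).
- Connector: *and*, in section 9.2.2 and in the synopsis.
- Women are eligible (inclusion 2). For them B is not applicable.

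**Step 1. Truth table**

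| Subject | A | B | As written (A and B) | Separate grounds (A or B) |
|---|---|---|---|---|
| Man | yes | yes | excluded | excluded |
| Man | yes | no | not excluded | excluded |
| Man | no | yes | not excluded | excluded |
| Man | no | no | not excluded | not excluded |
| Fertile woman | yes | not applicable | undefined | excluded |

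For men, the text excludes 1 of 4 combinations and separate grounds exclude 3 of 4. These are combinations, not people.

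**Step 2. Share of men with A who are excluded**

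Let q = P(B | A), the share of men unable to use contraception who also refuse the undertaking. As written, P(excluded | A) = q. With separate grounds it is 1. The protocol gives no q, so a range is assumed:

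| q (assumed) | Excluded as written | Excluded with separate grounds |
|---|---|---|
| 0.01 | 1% | 100% |
| 0.05 | 5% | 100% |
| 0.10 | 10% | 100% |
| 0.25 | 25% | 100% |
| 0.50 | 50% | 100% |
| 1.00 | 100% | 100% |

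**Step 3. The protocol's own usage**

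Exclusions 14, 15 and 17 each join two alternative grounds (heavy use of alcohol, tobacco or caffeine, and inability to stop) with *or*. Exclusion 18 stands beside them and uses *and*.

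**Step 4. Does another provision supply the requirement?**
- Exclusion 3 concerns women who are or may be pregnant, or are lactating. It does not ask for contraception.
- Urine hCG is tested at screening, on -1d and at the post-study visit, and also on phase 2 -1d in the food-effect cohort. A test detects pregnancy and does not prevent it. The final test falls 12 − 1 = 11 to 16 − 1 = 15 days after the dose in the single ascending dose cohorts, and 18 − 7 = 11 to 22 − 7 = 15 days after the last dose in the multiple-dose cohorts. That is well inside the three-month period. The tests do not concern partners of male subjects.
- Exclusion 19 is discretionary.

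None of these requires contraception during the study or for three months after it.

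**Step 5. Method list**

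The criterion speaks of contraception for subjects themselves or for their spouse or partner, but the intrauterine device line names only the spouse or partner. The barrier and surgery lines do reach female subjects. The mismatch is therefore confined to one item.

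**The case against.** The strongest reply is that the sentence can be read differently. The relative pronoun is repeated before the second condition, and in a list of exclusions this can describe two excluded groups. That is probably what was meant. The flow charts keep Korean column labels, so the English may be a translation, and a strict truth-table reading of one conjunction may be too severe. This stands as an account of intent, but it does not make the text clear: exclusions 15 and 17 repeat the same pronoun and use *or*.

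A reader might also infer more than the protocol supports:
- *That the rule excludes almost nobody who cannot use contraception.* This depends on q, which is not given.
- *That it cannot operate for women, or excludes none of them.* The result is undefined rather than certainly negative. A woman who gives no undertaking could be read as not agreeing, and the wording on subjects themselves and on barriers for either sex shows that women were meant to be covered.
- *That it is the only barrier to conception during dosing.* Dosing takes place in hospital, with discharge on 4d (single dose, each phase) or 10d (multiple dose), and exclusion 3 and the repeated hCG tests also apply. The gap is in the requirement for contraception, above all after discharge.
- *That all fertile subjects among the 88 are affected.* Someone who can use an accepted method and agrees not to donate sperm is treated the same under either reading.
- *That the method list ignores women.* The surgery line covers the person and names female procedures. If a woman's own intrauterine device is not credited, the list is stricter for her, not laxer.
- *That no embryo-fetal study exists.* The preclinical summary mentions none, but silence in a summary does not establish absence.

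**Conclusion.** The point holds as a drafting defect in an operative safety criterion. Taken literally, exclusion 18 requires both conditions before it excludes a man, and it leaves the outcome for an eligible fertile woman undefined. The partial backstops do not supply the missing requirement. In logical terms, 1 of 4 combinations is excluded for men where separate grounds would exclude 3. The number of people concerned is unknown: it comprises men who meet exactly one condition and fertile women unable to use contraception, and the protocol gives no basis for counting either.

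The conclusion rests on a literal reading of the connector and on the protocol alone; the consent form and investigator's brochure were not available and might state the requirement more clearly. It affects eligibility and subject protection, not any analysis.

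**What to change.** In section 9.2.2 and in the synopsis, state the two conditions as separate, independent grounds for exclusion over the period already specified: one for subjects unable to use an accepted contraceptive method, and one, applying to male subjects, for those who do not agree to refrain from sperm donation. The sponsor should also reconcile the intrauterine device line with the criterion's reference to subjects themselves and with the admission of women. Which methods are acceptable, and for whom, is a clinical decision for the sponsor and investigator, and this review does not propose one.

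The cost is a wording amendment in two places, with no added visit, procedure or subject.

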### 9.3. Withdrawal Criteria

'Enrollment' means that the subject who participated in the study (ie, signed the informed consent form) met the inclusion/exclusion criteria and was assigned a subject randomization number according to randomization. 'Dropout' means that an enrolled subject does not complete the study. Dropout could be decided at any time during the study period for the following reasons. Dropouts of enrolled subjects from the study should be reported on the eCRF with the date of the dropout, date of the last study drug administration and the reason for the dropout.

- 1) When it is judged that it is difficult for the subject to participate in a clinical study any longer due to a clinically unacceptable serious adverse event or abnormality such as a clinical laboratory test value
- 2) When the subject takes any medication that is expected to influence the safety and pharmacokinetic characteristics of investigational drug without the permission of the investigator
- 3) When the major protocol deviation significant enough to consider discontinuation of the study is identified during the study, such as the subject was found not to be eligible based on inclusion/exclusion criteria after enrollment.

- 4) When the subject does not wish to proceed with investigational drug administration or withdraws consent during the study period
- 5) When the subject does not visit on time and cannot be contacted
- 6) In the cases where the principal investigator or sub-investigator decides to withdraw the subject from the clinical study for other reasons

Those who drop out after administering the investigational drug visit the clinical study institution within 7 days if possible of the dropout (or the first recognition of dropout) and conduct an equivalent post-study visit. However, if the subject refuses to visit, if possible, concomitant medications and lists related to adverse events should be checked by phone. Also, if the dropped out subject has clinically significant abnormal test results, follow-up should be continued. Subjects who have been dropped out due to adverse events or deviations of safety standards should be followed up until symptoms subside and abnormal laboratory test values return to standard values, or there is a satisfactory explanation for the observed changes. If follow-up is not possible, it is considered as 'failed to follow up'.

If discontinued due to a serious adverse event, the serious adverse event should be reported in accordance with <13.3. Reporting of Serious Adverse Events>.

